### Recruitment and retention

Recruitment will include two emails that will be sent to more than 20,000 members of the organization with an invitation to visit the study website for more information. An advertisement for the study will also be posted on a website hosted by the organization that is devoted to research and study recruitment, with a wide circulation (>10,000 visitors monthly). Finally, will post targeted social media advertisements to individuals who report the organization as their primary employer on Facebook and LinkedIn.

Potential participants will be directed to an online landing page with more information about the study. An online screener will be automatically scored and used to determine eligibility according to the study inclusion/exclusion criteria, resulting in either an invitation to provide consent and complete the baseline procedure, or a message indicating they were not eligible. Due to the virtual nature of this study, consent was collected via electronic signature. Participants were informed they could stop at any time, and who had questions were encouraged to email or call the study team. Participant responses will be de-identified and results published in aggregate. No identifiable data will be disclosed to the employer.

After providing consent via the online landing page, participants were automatically randomized by a computer program. Due to the multiple steps necessary to enroll in the experimental arm, we weighted assignment to the experimental group 1.3 to 1 to ensure equal enrollment in each group.

All enrolled participants will receive $25 for completing the baseline procedures, a t-shirt ($10 value) for completing the first monthly sleep diary, and a $20 gift card for completing the end-of-study questionnaire. Each month, participants who complete the monthly questionnaire which they receive via email will be entered in a raffle to win one of two pairs of Bluetooth wireless headphones ($250 value each). Finally, for each study component completed, participants receive chances for a raffle of gift cards, ranging in value from $100 to $500, at the end of the study. Participants who are unresponsive to emailed questionnaires will receive up to 2 reminder follow-up emails.

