### Study arms

#### Experimental arm

After consenting, participants randomized to the experimental group will take a short online initial contact questionnaire to collect basic demographics. They will then view a 20-minute sleep health education video. Immediately after the presentation, the participant will be presented with a short sleep disorders risk assessment which displays the results upon completion, either high risk for a sleep disorder (obstructive sleep apnea, insomnia, or restless legs syndrome) or low/no risk a sleep disorder. Participants are then presented with a baseline questionnaire to assess sleep, health, and lifestyle. Finally, the experimental group participants will be invited to download the study app (“dayzz”). They will be encouraged to use the dayzz app throughout the study (up to 9 months, depending on date of enrollment).

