### Statistical plan

We plan to analyze anonymized data using an intention-to-treat approach (ITT). All outcome measures will be compared by assignment to the experimental and waitlist control groups in the primary analysis. The primary ITT analysis will include all participants who are randomized in the study. Secondary analyses will compare outcomes using an as-treated approach and an adherent to treatment approach. The as-treated approach will compare those who download dayzz to those who do not, regardless of their assigned randomization. We anticipate some cross-over between groups due to sharing of the app information among study participants. The adherent to treatment approach will exclude participants from the experimental group who did not engage with app throughout the study. We further plan to quantify temporal changes within participants assigned to the experimental group.

To evaluate changes in sleep behavior, we will examine the distribution of the data to determine if it meets assumptions for parametric tests. Assuming randomization has balanced known and unknown confounders and we observe a normal distribution, we will compare sleep duration between the groups using a t-test. We will use a rank sum test if the distribution is not normal. The distribution of the data will be examined, and transformations will be performed as necessary for valid comparisons. If potential confounders are not balanced between groups, we plan to use regression models with an appropriate link function and distribution to test all hypotheses. The number of healthy sleep changes at the end of the study will be compared between the groups using a rank sum test.

To evaluate changes in sleep quality, we will compare the proportion of participants with poor sleep quality according to the PSQI in the experimental group versus the waitlist control group using a chi-2 test. These continuous measures will be compared using a t-test. To examine changes in mood, alertness, and energy we will compare these ordinal variables using Wilcoxon rank sum tests between the experimental and waitlist control arms. We will estimate changes in absences and productivity using reported salary information and compare the cumulative cost of each using a t-test. We will estimate the incidence of crashes, near-crashes, and injuries which will then be compared using Poisson regression. Finally, we will compare cumulative healthcare costs over the study using t-tests.

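### The as-treated and adherent secondary analyses group participants by behaviour after randomisation, so they do not estimate a causal effect of the app; the primary ITT analysis is unaffected

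*Protocol article*

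**What the plan says.** All statements are in the protocol article. Under Statistical plan, the primary set is clear: "The primary ITT analysis will include all participants who are randomized in the study". The section continues: "Secondary analyses will compare outcomes using an as-treated approach and an adherent to treatment approach".

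- As-treated: "The as-treated approach will compare those who download dayzz to those who do not, regardless of their assigned randomization". It adds: "We anticipate some cross-over between groups due to sharing of the app information among study participants".
- Adherent: "The adherent to treatment approach will exclude participants from the experimental group who did not engage with app throughout the study". No matching exclusion is made among controls.

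The default tests are unadjusted (t, rank sum, chi-squared) plus Poisson regression. The t-test for sleep duration is premised on randomisation having balanced confounders. There is one general adjustment clause: "If potential confounders are not balanced between groups, we plan to use regression models with an appropriate link function and distribution to test all hypotheses".

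Two other sections bear on uptake. Under Experimental arm, the app comes after the education video, the risk assessment and the questionnaires: "Finally, the experimental group participants will be invited to download the study app". Under Recruitment and retention, because of those steps, "we weighted assignment to the experimental group 1.3 to 1 to ensure equal enrollment in each group".

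**The concern.** Downloading the app and continuing to use it happen after randomisation and are chosen by the participant. Both may go with motivation, baseline sleep, general health and willingness to answer questionnaires. The outcomes are self-reported and controls know they are waiting, so motivation can plausibly affect both app use and the answers given.

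The two analyses break the randomised comparison in different ways. As-treated pools experimental non-downloaders with controls and moves cross-over controls in with the users. It also mixes the components of the intervention: experimental non-downloaders may have seen the sleep education programme (SHAW), while cross-over controls have the app without it. The adherent analysis sets a selected part of the experimental arm against an unselected control arm.

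The plan itself expects incomplete uptake and cross-over. If ITT were null because of low uptake, a reader could turn to these two analyses for effectiveness among users, and nothing in the section cautions against a causal reading. The closing paragraph of the Discussion says that the trial's results will show whether the app is effective.

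**Working it through.** **The plan's own figure.** Power analysis states a detectable effect size of 0.16 with 500 per arm, without alpha, sidedness or power. With SD 1 the standard error is √(2/500) = 0.0632.

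- One-sided alpha 0.05, 80% power: (1.645 + 0.842) × 0.0632 = 0.157, which rounds to 0.16.
- Two-sided alpha 0.05, 80% power: (1.960 + 0.842) × 0.0632 = 0.177.

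The figure serves here only as a yardstick for the bias.

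**Null model.** The app has no effect. In both arms a share p are would-be users, whose mean outcome is g SD better than the others' for reasons unrelated to the app. In the experimental arm all of them download. In the control arm a share c of participants cross over, all from among the would-be users. N = 500 per arm is from the document; p, c and g are assumptions.

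*As-treated.* Downloaders number N(p + c), with mean g. Non-downloaders number N(2 − p − c), of whom N(p − c) are would-be users.

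- Bias = g − g(p − c)/(2 − p − c) = 2g(1 − p)/(2 − p − c)
- SE = √[1/(N(p + c)) + 1/(N(2 − p − c))]

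*Adherent*, with the engaged share equal to p. The engaged have mean g; all controls have mean gp.

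- Bias = g(1 − p)
- SE = √[1/(Np) + 1/N]

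Two-sided 5% rejection rate = Φ(bias/SE − 1.96) + Φ(−bias/SE − 1.96).

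Example, p = 0.70, c = 0.05, g = 0.3:

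- As-treated bias = 2 × 0.3 × 0.30/1.25 = 0.144; SE = √(1/375 + 1/625) = 0.0653; ratio 2.20; rejection 59.7%.
- Adherent bias = 0.3 × 0.30 = 0.090; SE = √(1/350 + 1/500) = 0.0697; ratio 1.29; rejection 25.2%.

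| Download (5% cross-over) | g (SD) | As-treated bias | Rejection | Adherent bias | Rejection |
|---|---|---|---|---|---|
| 50% | 0.2 | 0.138 | 49.5% | 0.100 | 25.2% |
| 50% | 0.3 | 0.207 | 83.2% | 0.150 | 49.1% |
| 70% | 0.1 | 0.048 | 11.4% | 0.030 | 7.1% |
| 70% | 0.2 | 0.096 | 31.2% | 0.060 | 13.8% |
| 70% | 0.3 | 0.144 | 59.7% | 0.090 | 25.2% |
| 90% | 0.1 | 0.019 | 6.0% | 0.010 | 5.3% |
| 90% | 0.3 | 0.057 | 14.7% | 0.030 | 7.5% |

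**Simulation check** (5,000 runs per scenario). At 70% download, g = 0.2 gave 30.0% as-treated and 13.8% adherent; g = 0.3 gave 60.2% and 26.0%. ITT rejected in 4.4% to 5.2% of runs across all scenarios simulated.

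**Weighted allocation.** Read the weighting as 650 v 500, take completion as 1/1.3 = 77%, equate that with download, and assume no cross-over. As-treated rejection is then 10.5%, 27.9% and 54.0% for g = 0.1, 0.2 and 0.3. The adherent rate is 6.5%, 11.3% and 19.5% with 77% engaged, and 12.3%, 34.8% and 65.3% with only 40% engaged.

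**Use driven wholly by motivation.** Suppose download is a strict cut on a motivation score that correlates 0.1, 0.2 or 0.3 with outcome (70% download, 5% cross-over, 40% engaged). As-treated rejection is 31%, 84% and 99%; adherent 21%, 64% and 93%. The cut implies gaps between downloaders and non-downloaders of 0.17, 0.33 and 0.50 SD. Halving the bias, as when motivation only partly drives use, brings these down to 11%, 31% and 60%, and 9%, 21% and 41%.

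**Opposite direction.** If would-be users have worse outcomes, g is negative and the bias keeps its size with the sign reversed. At 70% download and g = −0.3, a true benefit of 0.16 SD among downloaders would appear as 0.16 − 0.144 = 0.016.

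**The case against.** The strongest reply is the plan's hierarchy. ITT on everyone randomised is primary and both analyses are labelled secondary. That stands: a reader might infer that the trial's main conclusion is compromised, and the document does not support this.

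A reader might also infer that any gap between these analyses and ITT is pure selection. That is so only if the app has no effect. If it works, non-use and cross-over dilute ITT, and the results differ for that reason too. Nor must the bias favour the app; worse sleepers may be the likelier downloaders. And only the as-treated analysis compares users with everyone else; the adherent analysis leaves the non-engaged out altogether.

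On size, the highest rates need use to be fixed entirely by motivation, which nothing in the document supports. A claim that the bias reaches 0.16 SD at a correlation of 0.2 fails once use is only partly driven by motivation.

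The regression clause could reduce measured imbalance if applied to these groupings. It is conditional on imbalance in potential confounders and cannot reach unmeasured motivation.

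Finally, the analysis plan is not shown. It may well define engagement, so the lack of a definition here is not held against the plan. But the article states the comparison groups themselves, and those are the problem.

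**Conclusion.** The point holds for the two secondary analyses only. As written, they compare groups formed by behaviour after randomisation, carry no caution on causal reading, and can produce or mask an app effect while ITT keeps its 5% error rate.

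With no true effect, 70% download, 5% cross-over and a prognostic gap of 0.2 to 0.3 SD, the false-positive rate is about 30% to 60% as-treated and 14% to 26% adherent (70% engaged). At 90% download the as-treated rate is 6% to 15% for gaps of 0.1 to 0.3 SD. Rates are higher if use is driven wholly by motivation. Uptake, cross-over rate, gap and direction are all assumptions, so these are ranges and not predictions. The matter should be corrected, but it does not threaten the primary result.

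**What to change.** 1. Label the as-treated and adherent results as descriptive associations, with no efficacy claim.
2. Make the secondary effectiveness-among-users analysis a complier average causal effect with randomised assignment as the instrument: two-stage least squares, or the ITT difference divided by the arm difference in uptake. State it as the effect of receiving the SHAW-plus-app package. Assignment delivers both, so an instrument for download alone would credit the app with any effect of the video.

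With no effect of assignment the estimate is centred on 0, whoever chooses to use the app.

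**Data.** A reader might assume that everything needed is already collected; the document does not show this. The section on feasibility and acceptability collects app-usage data in the experimental group only, and nowhere is video viewing said to be recorded. Download status for controls, including cross-over, must be obtainable from system or developer records, as must video viewing if it enters the uptake definition.

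**Cost.** Wording, code and that data check. Intervals widen: with illustrative uptake of 70% v 5%, the ITT standard error is divided by 0.70 − 0.05 = 0.65, so 0.0632/0.65 = 0.097, about 1.5 times as large. The estimate is for the package and not the app alone, and a cross-over control who has the app without the video fits that definition imperfectly.

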### Power analysis

The power analysis was performed on the anticipated cohort of 1000 active participants providing adequate data for comparison (500 in each arm of the protocol). Power was estimated for each of the aims using GPower version 3.1.9.4. We will be able to detect slightly smaller effects for continuous variables compared to binary variables if we choose to dichotomize in the analysis (e.g. any motor vehicle crash vs. none). A sample size of 500 in each group will enable us to detect an effect size of 0.16 between the groups (even if the impact is small, we will be able to detect a significant difference). This effect size roughly translates to a relative risk of 1.20. If fewer participants enroll than we expect, we will still be able to detect a small difference in effect size if we enroll at least 600 participants.

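### Test choice and covariate adjustment depend on observed normality and balance, no time term is stated for repeated outcomes, and change over time is examined in one arm only

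*Protocol article*

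**What the plan says.** Three rules in the Statistical plan of the protocol article matter here.

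- **Choice of test.** For sleep duration, "we will compare sleep duration between the groups using a t-test", provided that randomisation is taken to have balanced confounders and the data look normal. Otherwise, "We will use a rank sum test if the distribution is not normal". Transformations may also be applied as needed once the distribution has been inspected.
- **Adjustment.** "If potential confounders are not balanced between groups, we plan to use regression models", and this clause covers all hypotheses. No covariates are named and no threshold for imbalance is given.
- **Time.** No between-arm test carries a time term. The only temporal analysis is this: "We further plan to quantify temporal changes within participants assigned to the experimental group".

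The data available are richer. Under Study arms, each participant in either arm completes one diary week in the first month and one in the third, and receives monthly questionnaires for up to 9 months. Sleep duration, mood, alertness and energy are on the diary. Mood, alertness, energy and work performance are on the monthly questionnaire. The Discussion says the trial will examine durability as well as effectiveness, and that it launched in August 2020.

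**The concern.** A t-test estimates a difference in means, a rank-sum test addresses whether one arm tends to have higher values, and a transformed analysis estimates an effect on yet another scale. If the data decide among them, nobody can say beforehand what the reported effect on sleep duration will be. Adjustment triggered by imbalance raises the same problem for every outcome: the decision to adjust, the covariates and the link function are all left until the data have been seen.

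In addition, a two-sample test on an outcome measured several times forces an unstated choice of occasion or average, and it cannot show whether an effect lasts. The planned temporal analysis does not fill that gap. A trend in the experimental arm alone, from August 2020 over up to 9 months, mixes any app effect with season and with the course of the pandemic. The waitlist arm supplies concurrent data of the same kind that would remove that confounding.

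**Working it through.** **Inputs from the protocol.** 500 per arm and a standardised effect of 0.16: "A sample size of 500 in each group will enable us to detect an effect size of 0.16 between the groups". Alpha, power and sidedness are not stated. **Assumptions.** Alpha 5%, 80% power where a detectable effect is computed, within-person correlation ρ from 0.3 to 0.7, and an effect that is constant over time.

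**1. The plan's own figure.** Detectable effect = (z_alpha + z_power) × √(2/n), with √(2/500) = 0.0632.
- One-sided 5%, 80% power: (1.645 + 0.842) × 0.0632 = 0.157, which rounds to the stated 0.16. Power at 0.16 is 81%.
- Two-sided 5%, 80% power: (1.960 + 0.842) × 0.0632 = 0.177. Power at 0.16 is Φ(0.16/0.0632 − 1.960) = Φ(0.570) = 71.6%.

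The figure therefore reproduces for an unadjusted two-sample comparison, but only one-sided. The two-sided value is the base below.

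**2. Does comparing means need normality at this size?** Under no effect, with 500 per arm and a covariate correlated 0.5 with the outcome (before the skewing transformation), 10,000 normal and 6,000 skewed (log-normal) data sets were simulated at a nominal 0.05:

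| Procedure | Normal | Skewed |
|---|---|---|
| t-test throughout | 0.049 | 0.046 |
| t-test or rank-sum by normality pretest | 0.049 | 0.049 |
| Adjust only if imbalance is significant | 0.043 | 0.040 |
| Most favourable of t, rank-sum, adjusted | 0.080 | 0.086 |

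The t-test holds its level on skewed data, so switching to ranks is not needed for validity. Applied mechanically, the plan's rules do not inflate type I error. Only free choice of the best result does.

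**3. Gain from using repeated measurements.** The variance of the mean of m occasions relative to one is v = (1 + (m − 1)ρ)/m, which for two diary weeks is (1 + ρ)/2. With baseline adjustment of a single follow-up value, v = 1 − ρ². Power = Φ(0.16/(0.0632√v) − 1.960).

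| ρ | Two diary weeks: v | Power | Clean baseline: v | Power |
|---|---|---|---|---|
| 0.3 | 0.65 | 88% | 0.91 | 76% |
| 0.5 | 0.75 | 83% | 0.75 | 83% |
| 0.7 | 0.85 | 78% | 0.51 | 94% |

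At ρ = 0.5 the two diary weeks give 0.16/(0.0632 × 0.866) = 2.92, and Φ(2.92 − 1.96) = 83%. One-sided, the same step goes from 81% to 90%.

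This gain belongs to the averaged effect. The arm-by-time contrast between the two weeks has relative variance 2(1 − ρ), which is 1.0 at ρ = 0.5. It answers the durability question but is no more precise than a single week.

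**4. Which baseline is usable?** Under Experimental arm the order is: initial contact questionnaire (demographics), video, risk assessment with displayed result, baseline questionnaire. Controls complete the same two questionnaires and receive the intervention only at the end. The baseline questionnaire thus follows part of the intervention in one arm only. The initial contact questionnaire precedes the video in the experimental arm and is clean in both. For diary sleep duration there is no pre-randomisation diary value at all, since both diary weeks come after enrolment.

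**The case against.** The strongest reply is that unadjusted two-group tests are valid in a randomised trial, that a normality pretest does no measurable harm to type I error, and that a mixed model is a preference for efficiency. A t-test on the average of the two diary weeks would also capture the gain in step 3. This is largely fair, and it limits the point. It does not give the plan a fixed quantity to estimate, and the article does not say that the weeks will be averaged.

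It can also be said that an article condenses a fuller plan. That covers omitted detail, but the conditional rules and the one-arm temporal analysis are what the article itself sets out.

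Several stronger readings are tempting, and the documents do not support them:

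- *Every outcome is compared post-only.* Crashes, near-crashes and injuries go to Poisson regression, costs are cumulated over the study, and the tests seldom name a timepoint. Healthy sleep changes are a checklist of changes made since joining, so they have no baseline. The timing of the PSQI is not stated.
- *Baseline adjustment is precision for free.* Step 4 shows otherwise: adjusting for a baseline questionnaire completed after the video and risk result in one arm could bias the effect.
- *The within-arm trend will be presented as a treatment effect.* The primary analysis compares all outcomes by assignment, and the trend is only to be quantified.
- *Participants with missed months will be dropped.* The article does not say how missing months are handled, and that detail may sit in a fuller plan.

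**Conclusion.** The point holds in limited form. The analysis of sleep duration, and the use of adjustment for any outcome, are not fixed in advance, so the estimand can change with the data for no gain in validity at about 500 per arm. Outcomes measured repeatedly in both arms have no stated time term. The one temporal analysis planned cannot address durability, because it leaves out the concurrent control arm.

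The size is moderate. For diary outcomes, joint use of both weeks would raise power at 0.16 from about 72% to between 78% and 88%, or 83% at correlation 0.5. This rests on assumed correlations, two-sided 5% testing, 500 analysed per arm, a constant effect, and a plan that would otherwise use a single week. The baseline-adjusted figures (76%, 83% and 94%) apply only if a clean baseline exists, which the present sequence does not provide for questionnaire values. The randomised comparisons stay valid, so this is a change that should be made and not a fatal flaw.

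**What to change.** Specify one model per outcome type, whatever balance or normality is observed:

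- Use a linear mixed model, or its ordinal or logistic equivalent, on all scheduled follow-up measurements from both arms, with arm, time and arm-by-time.
- Include a fixed list of covariates from the initial contact questionnaire, which precedes the video, and drop the imbalance trigger.
- Keep the rank-sum test as a sensitivity analysis.
- Replace the experimental-arm-only trend with the between-arm arm-by-time contrast, and tie it to the durability aim.
- Leave the Poisson and cumulative-cost outcomes on their own models.

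This costs analysis wording and code, with slightly more modelling work and no new data. Demographic covariates alone may add little precision; most of the gain comes from joint use of the repeated measurements. Adjusting for baseline questionnaire values is a separate step. It should be done only if those values are collected before the video and risk result in both arms, which is a procedural change and not just code.

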#### Control

Participants assigned to the waitlist control condition will, at baseline, complete the same initial contact and baseline questionnaires. Participants in the waitlist control group will complete the eDiary and monthly and end-of-study questionnaires. At the end of the study, waitlist control participants will receive the intervention (SHAW and dayzz app).

Each participant will also complete a daily electronic sleep diary (eDiary) sent via email for one week within the first month of enrollment and for one week within the third month of the study. For up to 9 months following the baseline procedure, on the 28th of each month, each participant will receive an email with a link to the monthly questionnaire. At the end of the study, each participant will receive a link to complete the end-of-study questionnaire. The eDiary and all questionnaires are completed online. This study was approved by the Partners HealthCare Institutional Review Board (IRB) on February 10, 2020 (Protocol #: 2019P003277). Please see the Fig 2 for a flow chart describing the study procedures. Per the IRB, a Data Safety Monitoring Board was not required for this clinical trial.

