#### Adverse health and safety outcomes

Motor vehicle crashes and near-crashes will be captured via self-report on the monthly questionnaire, consistent with previous studies [7,20]. Participants will be asked, “In the last month, did you have any motor vehicle accidents or crashes (actual collisions) in which you were driving,” and “In the last month, did you have any near miss motor vehicle accidents or crashes (narrowly avoided property damage or bodily harm) in which you were driving.” Participants who responded yes will then be asked to provide the number of times that each outcome occurred during the month. We will also assess injuries by asking participants “In the last month, how many injuries did you have” and attentional failures by asking participants the number of times they “Nod off or fall asleep during meetings at work,” “…on the telephone,” “…while driving,” and “…while stopped in traffic.”

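### Poisson regression is named for repeated monthly safety counts with no stated allowance for differences in risk between people; with default standard errors the tests for near-crashes and injuries could be well above 5%

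*Protocol article*

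**What the plan says.** The Statistical plan section gives one sentence to the analysis of these events: "We will estimate the incidence of crashes, near-crashes, and injuries which will then be compared using Poisson regression". It names no unit of analysis, person-time offset, dispersion term or variance estimator, and it excludes none of these.

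The Adverse health and safety outcomes section shows that the data are counts. "Motor vehicle crashes and near-crashes will be captured via self-report on the monthly questionnaire", and for crashes and near-crashes, "Participants who responded yes will then be asked to provide the number of times that each outcome occurred during the month". Injuries are asked for directly as a number: "In the last month, how many injuries did you have".

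The Control section, in a paragraph that covers both arms, sets the repetition: "For up to 9 months following the baseline procedure, on the 28th of each month, each participant will receive an email". The Experimental arm section adds that the length of app use, at most 9 months, depends on when a person enrolled, so the number of monthly reports will vary between people.

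Two other statements bear on the point. The Statistical plan allows regression with another link and distribution, but only if potential confounders turn out unbalanced. The Power analysis section keeps open the option of analysing a binary outcome, any crash against none.

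**The concern.** Poisson regression with its default standard errors takes the variance of a count to equal its mean. For totals within an arm, that means everyone with the same follow-up shares one event rate. If some people carry more risk than others, the totals vary more than the model assumes, the standard error is too small, and the confidence interval is too narrow.

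The clause on link and distribution does not cover this. It is triggered by imbalance between arms, whereas extra-Poisson variation is spread within each arm and is present under perfect balance.

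At stake is the error rate of the safety comparisons. A chance difference in near-crashes or injuries could be reported as a safety benefit or a harm of the app. The Statistical plan puts all outcome measures into the primary intention-to-treat comparison, and the Discussion says that observed improvements would be strong evidence.

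**Working it through.** **The plan's own figure.** The plan states no figure for the Poisson analysis. Its only design figure is in Power analysis: "A sample size of 500 in each group will enable us to detect an effect size of 0.16 between the groups". Alpha, sidedness and power are not given. The value follows from an assumed one-sided 5% test with 80% power: (1.645 + 0.842) × √(2/500) = 0.157. It plays no part in what follows. The check uses only the 500 per arm.

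**Formula.** Let E1 and E0 be the total events in the two arms. With arm as the only covariate, the model-based standard error of the log rate ratio is √(1/E1 + 1/E0), whether the rows are person-months or person totals with an offset. If the variance of a person's total is V times its mean, the true standard error is √V times larger. The true size of a nominal two-sided 5% test is then 2 × [1 − Φ(1.96/√V)].

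| V | true SE / model SE | true size | coverage of 95% CI |
|---|---|---|---|
| 1.0 | 1.00 | 5.0% | 95.0% |
| 1.25 | 1.12 | 8.0% | 92.0% |
| 1.5 | 1.22 | 11.0% | 89.1% |
| 2 | 1.41 | 16.6% | 83.4% |
| 3 | 1.73 | 25.8% | 74.2% |

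**What V depends on.** If people's rates vary around the arm mean with relative variance θ, and the mean total per person is μ, then V = 1 + θμ. Both θ and μ are assumptions here. Reaching V = 1.5 needs θμ = 0.5. Over 9 months that means θ = 0.5/0.9 = 0.56 at 0.10 events per month, θ = 0.5/0.45 = 1.1 at 0.05 per month, and θ = 0.5/0.045 = 11 at 0.005 per month. Common events are therefore exposed and rare ones hardly at all.

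**Is θ zero?** The article's Introduction says no. It reports that 30–40% of employees screen positive for a sleep disorder and cites an 83% higher incidence of adverse safety outcomes in hospital workers who did. With 35% positive, the mean relative rate is 1 + 0.35 × 0.83 = 1.29, the variance is 0.35 × 0.65 × 0.83² = 0.157, and θ = 0.157/1.29² = 0.09. At μ = 0.9 this gives V = 1.085 and a size of about 6%. That factor alone is minor, but it rules out a single shared rate. Driving exposure could add more. If, as an assumption, half the participants hardly drive and the rest have twice the mean rate, θ = 1, so V = 1.9 at 0.10 near-crashes per month.

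**Simulation under no true difference.** 20,000 trials, 500 per arm, 9 months each, gamma person effect:

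| Event (assumed monthly rate) | θ | V | model-based size | robust size |
|---|---|---|---|---|
| Crash (0.005) | 0 | 1.00 | 4.4% | 4.4% |
| Crash (0.005) | 4 | 1.18 | 6.7% | 5.1% |
| Injury (0.05) | 0 | 1.00 | 5.1% | 5.1% |
| Injury (0.05) | 1 | 1.45 | 10.2% | 4.9% |
| Injury (0.05) | 4 | 2.80 | 24.1% | 5.1% |
| Near-crash (0.10) | 0 | 1.00 | 4.9% | 4.9% |
| Near-crash (0.10) | 1 | 1.90 | 15.4% | 5.2% |
| Near-crash (0.10) | 4 | 4.60 | 36.3% | 5.1% |

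A second simulation (4,000 trials, follow-up uniform over 5 to 9 months, θ = 2) gave model-based sizes of 8.6%, 13.0%, 20.3% and 32.0% at 0.02, 0.05, 0.10 and 0.20 events per month. Robust errors gave 4.8% to 5.6%.

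**The case against.** The strongest reply is that the plan does not fix the faulty version. Poisson regression with robust standard errors is still Poisson regression and fits the sentence as written. The variance estimator is often left to a full protocol or analysis plan, neither of which is shown. The plan also intends to examine distributions, though it says so in the paragraph on sleep behavior, and a transformation would not repair a Poisson variance. The binary option for crashes would give one value per person and avoid the problem.

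Most of this stands, and it limits the point in four ways.

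- A reader might infer that all three safety comparisons are bound to be anti-conservative. The documents do not support that, because they do not commit to model-based errors.
- A reader might infer that repeated counts alone make the errors too small. They do not: with θ = 0 the test keeps its level (4.4% to 5.1%).
- Crashes cannot be grouped with the other two events. If they are rare, the inflation is slight.
- A reader might extend the point to nodding off and other attentional failures, but the plan names no Poisson analysis for them, so there is nothing there to correct.

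What does not stand is the reply that this is only a missing detail. The plan names a model whose default variance assumption conflicts with the article's own evidence that risk differs between people, and the only flexibility it states is tied to confounder imbalance.

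**Conclusion.** The point holds in conditional form. If model-based Poisson errors are used, the size of a nominal 5% test rises to about 11%, 17% and 26% at variance-to-mean ratios of 1.5, 2 and 3. That part is arithmetic. Where each outcome falls is not known, because the article gives neither event rates nor between-person variance.

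At assumed rates of 0.05 to 0.10 per month and a person-effect variance of 1 to 4, injuries and near-crashes come out at roughly 10% to 36%. Crashes reach about 7% at 0.005 per month and about 9% at 0.02. The estimated rate ratio itself is not distorted by the overdispersion; only its standard error, interval and p-value are.

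The importance is moderate. These events are among many outcomes, none is named primary, robust errors are not ruled out, and the problem can be repaired at analysis without new data.

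**What to change.** Replace the Poisson sentence in Statistical plan with wording such as:

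> For crashes, near-crashes and injuries, each participant's total count will be compared between arms by Poisson regression with the log of months reported as offset and robust (sandwich) standard errors.

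A negative binomial model with the same offset is an acceptable alternative. Choose one before the data are seen. The robust version keeps the model already named and held its level in every simulated scenario, including crashes at 0.005 per month (500 × 0.045 = 22.5 expected events per arm). The offset is needed because follow-up varies; without it, differences in months reported enter the counts as further variation.

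The cost is one sentence and one software option. Confidence intervals widen by a factor of about √V, that is 1.22, 1.41 and 1.73 at V = 1.5, 2 and 3. This is the width they should have.
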